### Primary outcomes

The primary outcome is the proportion of study participants provided with praziquantel drug (treatment coverage) and geographical cluster (a service area of the community health workers) in the intervention and control arms.

### Secondary outcomes

Secondary outcomes are:-Community Health Workers (CHWs) ability to use the POC-CCA rapid test accurately and safely.Community members acceptability (these are people’s perceptions and attitude on the two-treatment approach) of the POC-CCA test results offered by community health workers.Experience of Community Health Workers on the use of the POC-CCA rapid diagnostic test.Prevalence of *S. mansoni* infection based on the POC-CCA test conducted by Community Health Workers.

### Study population and inclusion criteria

Individuals aged 18 years and older residing at Kome Island were enrolled after written informed consent was obtained. Participants were enrolled in the study if: (i) aged 18 years and above (ii) willing to participate and give written informed consent and (iii) living in the study area. Participants were excluded from the study if: (i) pregnant at the time of treatment (ii) history of adverse reaction to praziquantel and (iii) present with serious conditions at the time of treatment and not deemed fit to take treatment.

### Sample size

The sample size was estimated using a simplified formula by Hayes and Bennet for cluster randomized trials [28], with a power of 80% to detect an absolute difference in proportion of adult individuals participating in mass drug administration of 25% (50% versus 75%) between the two arms with alpha of 5% and assumed coefficient of variation of 0.3616. The coefficient of variation of 0.3616 was used to account for unequal cluster size. In the intervention arm, we take 75% as level of treatment coverage recommended by WHO at community level [9]. A minimum estimated sample of 150 individuals for each cluster for 30 clusters giving an overall total of 4500 individuals (2250 interventions, 2250 controls) were needed to answer the research questions assuming the standard deviation between clusters of 0.226. For this study, cluster was defined as the service population of the community health worker.

### Training of community health workers on how to perform point-of-care circulating cathodic antigen test and use of praziquantel dose pole

Community health workers attended a three-day training on schistosomiasis, covering topics that included epidemiology, the national neglected tropical diseases control program and mass drug administration approach (school-based versus community-based treatment approach), causes, signs and symptoms of intestinal schistosomiasis and standard operating procedures of the study. In addition, CHWs were trained on how to dispense praziquantel drugs using the praziquantel dose pole, based on the height of the study participants and how to record the number of tablets/pills provided to each participant (Fig. 3). The CHWs were also trained on how to handle any side effects observed later or immediately after taking the treatment.

**Fig. 3 Fig3:**
[figure not shown]
Training and showing community health workers on how to measure height of participant and decide on the number of tablets to give based on height using the Praziquantel Dose pole at Kome Island, north-western Tanzania (The PI teaching CHWs)

Community health workers in the intervention arm attended one day of additional training covering how to perform and interpret the rapid test for intestinal schistosomiasis (Fig. 4). The topics covered included; how to request urine samples from participants, adherence to safety measures (wearing gloves before collecting urine containers with urine and washing used urine containers using provided disinfectants), urine safety and handling urine samples after analysis, labelling of the urine containers and test kits with specific study identification numbers, how to add urine sample to the test kit, interpret the result of the test (based on colour changes after 20 mins) and recording the results in the registry booklets provided. The training involved lectures, group discussions and demonstration by a qualified laboratory technician followed by practical sessions (Fig. 5). Community health workers practiced all the areas on which they were trained. After training, CHWs were given a spot examination to assess their ability to interpret the POC-CCA test. Used POC-CCA test kits from a previous study with positive, negative and unused test were given to CHWs for interpretation. The results of the spot examination are shown in Table 3.

**Fig. 4 Fig4:**
[figure not shown]
Training community health workers on the principal of Point-of-Care Circulating Cathodic antigen tests at Kome Island, north-western Tanzania (the PI teaching CHWs)

**Fig. 5 Fig5:**
[figure not shown]
**a** Laboratory technician demonstrating to community health workers on how to follow procedures of performing a POC-CCA test safely and accurately and (**b**) Practical class of community health workers after demonstration class at Kome Island, north-western Tanzania

**Table 3 Tab3:** Shows the performance of the spot test of community health workers after training on the preparation and interpretation of the Point-of-Care Circulating Cathodic Antigen tests

Test kit ID	Expert laboratory technician		Community health workers (CHWs)		Total marks for each test kit for CHWs (%)
	Positive	Negative	Positive	Negative	
122	Positive		Positive		100
14		Negative		Negative	100
60	Positive		Positive		100
d16	Positive	Negative	Positive		100
20	Positive			Negative	97
53	Positive		Positive		93
17	Positive		Positive		100
118		Negative		Negative	80
93		Negative	Positive		100
100	New test (unused kit)		New test(unused kit)		70

After the training, all community health workers were provided with praziquantel dose poles, registry booklets, writing materials and praziquantel drugs. In addition, community health workers in the intervention arm were provided with gloves, buckets, urine containers and point-of-care circulating cathodic antigens tests.

### Training of laboratory technicians on how to assess ability of community health workers to use

Two laboratory technicians were trained on how to assess the ability of trained CHWs in the intervention arm to adhere to the safety procedures and standard operating procedures of performing the POC-CCA test. The laboratory technician acted as an observer, visited the study sites (clusters) at two, four and six weeks post-training to assess CHWs using a standardized checklist (steps of test preparation and safety measures) as shown in Table 2. On site re-training was organized for poorly assessed CHWs.

### Data collection and follow-up

#### Recording of demographic information of participants and community mobilization

Trained CHWs in both arms recorded all demographic information of the study participants in the provided booklets. Collected demographic information included age, sex, sub-village of residence and history of taking anti-schistosomiasis treatment.

#### Diagnosis of *Schistosoma mansoni* infection using circulating-cathodic antigen test by community health workers

Trained CHWs in the intervention arm diagnosed study participants for *S. mansoni* infection using a commercially available test, the Point-of-Care Circulating Cathodic Antigen test (Rapid Medical Diagnostics, Pretoria, South Africa, Batch number: 170914118), a rapid test for intestinal schistosomiasis [29, 30](Fig. 6). Recording of the results was based on qualitative observation of color change of the test as per manufacturer instruction [29, 30]. Trace reactions of the test are considered positive [30]. After training, CHWs were provided with CCA test kits, urine collection containers, a copy of the job-aid (how to perform the test), examination gloves, disinfectants and disposal boxes. Community Health Workers (CHWs) were instructed to keep all the used POC-CCA tests (either with positive and negative results). Used test kits were collected on weekly basis and re-examined by a qualified laboratory technician as part of the quality check-up.

**Fig. 6 Fig6:**
[figure not shown]
Community health workers in the intervention arms (**a**, **b**, **c**, **d**) were involved in diagnosis of intestinal schistosomiasis using the POC-CCA test in different study clusters at Kome Island, north-western Tanzania

#### Praziquantel treatment coverage and drug inventory

In both arms, CHWs were provided with praziquantel drugs, praziquantel dose pole and treatment registry books. In the registry book, CHWs in the intervention arm, recorded the POC-CCA test results, the number of tablets/pills provided to each of the participant(s) based on the test results and any reported side effects. In the control arm, CHWs recorded the number of tablets/pills provided to each study participant and any side effects reported by participants.

Diagnosis of intestinal schistosomiasis and provision of PZQ drugs was done at an agreed site within a cluster. Tablets were swallowed under direct observation (DOT) of CHWs. Estimation of number of PZQ tablets given to each participant was done using the praziquantel dose pole, based on the height of an individual (Fig. 7). Study participants who experienced any mild adverse side effects were counselled at the treatment premises and cases with severe adverse effects, were referred to the nearby health facilities.

**Fig. 7 Fig7:**
[figure not shown]
Community health workers in the intervention arms taking height of the study participant to decide on the number of praziquantel pills to prescribe to participant after diagnosis at Kome Island, north-western Tanzania

#### Assessment of the community acceptability of the use of point-of-care circulating cathodic antigen by community health workers

A qualitative research approach using Focus Group Discussions (FGDs) was used to assess community acceptability of the approach. Eight community clusters out of 30 community clusters were selected (6 in each intervention arms and 2 control arms). In each of the cluster, one (1) FGDs session was conducted giving a total of 8 FGDs sessions. Each FGD consisted of 8–10 participants in each cluster. These FGDs participants included only those who participated in the study from the two arms. Focus Group Discussion participants were mobilized by CHWs from their respective cluster community and FGDs was conducted at a selected area near the cluster community. The interview guide was used as a tool to collect information on trust and confidence in CHWs, community willingness and acceptability of both approaches. For the intervention arm, additional information was collected on CHWs use of CCA rapid tests and trust of the test results from CHWs, compliance to treatment given and stigma associated with requesting urine samples from adult participants. The interviewer and the note taker were social scientists, speaking Kiswahili and the vernacular fluently. Table 4 shows the key questions which were used to stimulate the discussion.

**Table 4 Tab4:** Key questions which were used to stimulate discussion with community members in the intervention and control arms

In the intervention arms	
1	How did you feel, being diagnosed by a trained person you knew?
2	How did you feel when the community health worker asked you to bring urine samples for diagnosis?
3	Did you feel any stigma when asked by the community health worker to submit urine samples for diagnosis of intestinal schistosomiasis?
4	How did you feel when the community health workers told you that you were infected with intestinal schistosomiasis?
5	Did you agree with the test results or did you have any doubt on the test results? If you had any doubt, what were your concerns on the results given?
6	After being told you had the infection and given drugs, did you take/swallow the drugs given?
7	Did you experience any mild side effects after taking the drugs administered by the community health worker? If yes, what were the side effects experienced?
8	In general, what are your perceptions on the test or the exercise of diagnosis and treatment offered by community health workers?
In the Control arm	
1	How did you feel to be treated/receive drugs without being diagnosed if you had intestinal schistosomiasis?
2	How did you feel when the community health worker used a praziquantel pole to decide on the dosage or number of drugs to give?
3	Did you agree to take the number of pills given after the community health worker measured your height and decided on the number of pills without diagnosing you if you had intestinal schistosomiasis?
4	Did you experience any mild side effects after taking the drugs administered by the community health worker? If yes, what were the side effects experienced?
5	In general, what are your perceptions on the mass treatment without diagnosis test or the exercise of treatment without diagnosis offered by community health workers?
6	What are your recommendations on the exercise of treatment without diagnosis offered by community health workers at your village/community?

#### Exploring the experience of community health workers after using point-of-care circulating cathodic antigen rapid tests

Focus Group Discussions with CHWs were conducted at the end of the study. A guide was used to stimulate the discussion and the discussion focused on their experience on using the CCA kits and provision of treatment after diagnosis, what were the challenges during MDA, what were the opportunities and what were the perspectives of the participants on the exercise, participants trust of the results and their recommendations to improve the MDA exercise with and without a diagnostic component. Table 5 shows the key questions which were used to stimulate the discussion.

**Table 5 Tab5:** Key questions which were used to stimulate discussion with community health health workers in the intervention and control arms

In intervention arm	
1	What are the experiences and challenges you faced during the diagnosis and treatment of intestinal schistosomiasis exercise?
2	What opportunities did you take advantage of?
3	What are the perspectives of other community members regarding the test/diagnosis and treatment?
4	What recommendations do you have to help improve the test and treat exercise?
In control arm	
1	What are the experiences and challenges you faced during the treatment of intestinal schistosomiasis without diagnosis?
2	What opportunities did you take advantage of?
3	What are the perspectives of other community members regarding the treatment exercise without diagnosis?
4	What recommendations do you have to help improve the treat exercise without diagnosis?

#### Assessment of safety and accuracy of the circulating cathodic antigen (CCA) test performed by community health workers

A trained observer visited each of the CHW in the intervention arm at one, two and six weeks post-training and used a standardized checklist (Tables 4 and 5) to assess the performance of each CHW in adhering to safety procedures and procedures of performing the test, interpretation of the test results and recording of the test result. The observer also collected all the tests kits used within the week and sent them to a second observer to evaluate the test results. In addition, the field observer took a photograph of 20 POC-CCA tests with positive, negative and invalid result to assess CHWs ability to read CCA test accurately.

Observers were trained on how to use the check list and instructed on how to minimize observer bias. Using the checklist, the observer noted if CHWs performed each step correctly and also noted if she/he missed observing any step. The steps were divided into two parts, (i) those critical to safety and (ii) accurate performance of the test. Safety was defined as correctly wearing gloves, use of new urine container for every participant and disposal of the urine containers in approved buckets and urine samples in the toilet immediately after use. Whereas accuracy was defined as following all the necessary steps correctly to arrive at a correct diagnosis (i). Collecting urine samples in an enclosed pipette and pouring it in a test kit well (ii). Dispensing 2–3 drops of clearing buffer into the sample well (if provided by the manufacturer) (iii). Waiting for 15 min before reading test results (iv). Reading test results correctly (v). Recording the results. At each observation, the observer recorded number of POC-CCA rapid test performed since the previous visit and collected the used test kits, number of positives and number of treated participants. In addition, the observer recorded any challenges or concerns experienced by CHWs.

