**Fig. 2 Fig2:**
[figure not shown]
Flow diagram of trial design and number of sub-villages

**Table 1 Tab1:** Summary of the study profile

Study design	Cluster randomized controlled community trial
Intervention	Community health workers testing for *Schistosoma mansoni* infection using Point-of-care Circulating Cathodic Antigen test before offering treatment
Control	Mass drug administration using praziquantel without testing for *Schistosoma mansoni* infection as per current practice
Primary outcome	Proportion of study participants provided with praziquantel drug (treatment coverage) and geographical cluster (a service area of the community health workers) in the intervention and control arms
Cluster eligibility criteria	Having more than 60 adult individuals served by two community health workers
Inclusion	Individuals aged ≥18 years residing in a study cluster (s), willing to participate and give written informed consent
Exclusion	Pregnant women at the time of treatment, history of adverse reaction to praziquantel and acutely ill at the time of treatment
Sampling eligibility criteria	Residents of the selected clusters or residents of Kome island
Sampling exclusion criteria	Non-resident of the cluster or Kome island as identified by community health workers participating in the study
Sample size per arm	Total sample size (*N* = 4500), Intervention arm (n = 2250) and control (*n* = 2250)

To assess CHWs ability to use the POC-CCA test safely and accurately in the intervention arm, a trained observer (a laboratory technician) visited the study cluster at two, four and six weeks post-training and used a checklist to assess CHWs compliance to safety procedures (Table 2).

**Table 2 Tab2:** Shows the steps required to correctly and safely prepare a Circulating cathodic Antigen rapid diagnostic test

S/no	The steps required to correctly and safely prepare a circulating cathodic antigen test (Critical steps in noted boldface type)	Score
1	Prepare the diagnostic table (cover it with a plastic cover), assemble new test, pippete and gloves	
**2**	**Put on a pair of gloves**	
3	Provide participants with new urine container (s) and instruct them on how to collect urine sample(s) using the provided container	
4	Recording participants demographic information (name, age, sex and village of residence) in the registry when submitting urine sample (s) at the diagnostic table	

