**5**	**Receive urine sample from participant (s) label the container with participants identification number and place it in a sample collection dish**	
**6**	**Take Point-of-Care circulating cathodic antigen test kit (s), label it with participants (s) identification number which is similar to the one written on the urine container**	
7	Place the labelled point-of-care circulating cathodic antigen test kit on the table (level surface)	
**8**	**Take the urine container with identification number similar to the one labelled on the point-of-care circulating cathodic antigen test kit and collect urine sample using the enclosed pipette and pour 1–3 drops of urine sample in a test kit well**	
**9**	**Dispose the used pippete in a waste bucket immediately after pouring the urine sample in a test kit**	
**10**	**Dispense 2–3 drops of clearing buffer if provided in a sample well**	
**11**	**Wait for 15–20 min before reading the POC-CCA test result (either positive or negative)**	
**12**	**Read the result correctly (either negative or positive)**	
13	Record the result of the POC-CCA test in the participant register book	
14	Give the test result (s) to participants, and based on the test result, advise them (either to take treatment if results are positive or no treatment if negative)	
15	Dispose of used gloves, desiccant, wrappers and used test kits.	

The bolded sentences shows the most critical steps during preparation and use of the point-of-care circulating cathodic antigen test

At baseline, a quantitative questionnaire was used to collect data on CHW’s and community member’s (heads of households) knowledge about schistosomiasis, the previous community-based MDA strategy, acceptability to be diagnosed for intestinal schistosomiasis by CHWs and treatment with PZQ without being diagnosed for the targeted infection. At the end of the study, qualitative Focus Group Discussions (FGDs) were conducted to assess the experiences of CHWs from both arms after participating in the trial. FGDs were held with selected community members who participated in the study to assess community acceptability and attitudes towards use of POC-CCA test by CHWs.

Randomization of clusters to either intervention or control arms was based on the population size of the adult individuals served by a community health worker. All CHWs serving clusters with less than 60 adult populations were excluded from the study.

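### The assessment of CHW safety and accuracy contradicts itself on visit weeks and on used test kits, and defines safety by items the checklist does not record

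*Protocol article*

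**What the plan says.** The ability of CHWs to use the POC-CCA test accurately and safely is the first secondary outcome listed in the protocol article. It is measured in the intervention arm only, by an observer with a checklist.

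- **Visit weeks.** The trial summary, just before Table 2, says the observer "visited the study cluster at two, four and six weeks post-training and used a checklist". The section on training laboratory technicians agrees: "visited the study sites (clusters) at two, four and six weeks post-training". The section that defines the assessment says "at one, two and six weeks post-training and used a standardized checklist (Tables 4 and 5").
- **Used kits.** Table 2, step 15 reads "Dispose of used gloves, desiccant, wrappers and used test kits". The section on diagnosis says CHWs "were instructed to keep all the used POC-CCA tests", for weekly collection and re-examination, and the assessment section has the observer collect them.
- **Definition of safety.** The assessment section requires correct use of gloves, "use of new urine container for every participant and disposal of the urine containers in approved buckets", and disposal of urine in the toilet.
- **Analysis.** Under data management and analysis, the percentages of total, crucial and non-crucial steps done correctly are calculated for each observation cycle. A GEE logistic model is then fitted to correct performance of at least 90% of all steps.

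**The concern.** A step score is interpretable only if the time of observation, the scoring rule and the list of scored items are each fixed once. Here the timing is given in two versions. One scored step conflicts with a standing instruction to the people being scored. Part of the safety definition has no item to record it.

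At stake is the evidence on whether CHWs can do the test safely and accurately, which is a stated secondary objective. Change in performance over the weeks after training cannot be described if those weeks are uncertain. A step that penalises compliance would lower the scores for a reason unrelated to skill. Poorly assessed CHWs are re-trained on site, so mis-scoring could also alter what happens between visits.

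**Working it through.** The plan states no figure for this point that could be reproduced. The check sets the passages side by side and adds simple arithmetic on the 90% rule.

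**1. Visit weeks, in order of cycle**

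| Cycle | Trial summary; technician training | Assessment section | Difference |
|---|---|---|---|
| 1 | week 2 | week 1 | 1 week |
| 2 | week 4 | week 2 | 2 weeks |
| 3 | week 6 | week 6 | none |

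Weeks 2 and 6 appear in both schedules, but week 2 is the first visit in one and the second visit in the other. Only the third cycle has a settled time.

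**2. Used kits and the 90% rule**

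Inputs: Table 2 has 15 steps. Eight are in bold as critical (2, 5, 6, 8, 9, 10, 11, 12) and seven are not (1, 3, 4, 7, 13, 14, 15). The threshold is 90% of total steps.

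- Steps needed: 0.9 × 15 = 13.5, so 14.
- Step 15 lost: 14/15 = 93.3%, which passes.
- Step 15 and one other lost: 13/15 = 86.7%, which fails.
- Non-critical score with step 15 lost: 6/7 = 85.7% at best.

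Step 10 (buffer) applies only if buffer is supplied. Without it there are 14 steps, and 0.9 × 14 = 12.6, so 13 are needed. One lost step gives 13/14 = 92.9% (pass) and two give 12/14 = 85.7% (fail). The conclusion is the same.

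To show what having no margin means, assume that each remaining step is done correctly, independently, with probability p. This is an assumption and does not come from the document. With step 15 scored like any other step, the chance of meeting the rule is P(at least 14 of 15) = p^15 + 15 × p^14 × (1 − p). With step 15 always lost, it is p^14.

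| p | Step 15 like the others | Step 15 always lost |
|---|---|---|
| 1 | 1 | 1 |
| 0.98 | 0.965 | 0.754 |
| 0.95 | 0.829 | 0.488 |

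**3. Safety definition against the checklist**

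| Part of the definition | Item in Table 2 |
|---|---|
| Gloves | step 2 |
| New container per participant | step 3 |
| Disposal of containers | none |
| Disposal of urine | none |

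Step 9 concerns the pipette, and step 15 concerns gloves, desiccant, wrappers and kits. Two of the four parts are therefore not recorded.

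**The case against.** The strongest reply concerns the kits. CHWs also received disposal boxes, and a kit placed in a box that is later collected can count as both disposed of and kept. The observer who completed the checklist also collected the kits, so knew they were being retained. This stands as far as it goes: nothing shows that a retained kit was marked wrong. But no scoring rule settles the matter either, and read literally the two passages conflict.

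The analysis section names no separate safety score, only total, crucial and non-crucial steps. That is also correct. Yet safety is part of the named outcome and is expressly defined, so as defined it cannot be scored from the checklist.

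A reader might infer more than the document supports:

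- **That an obedient CHW fails the 90% rule, or loses a point at every visit.** One lost step still passes, and actual scoring of retained kits is not described.
- **That every observation is wrong.** Multiplying 2250/150 = 15 clusters by two CHWs and three visits gives 90, but this assumes that every CHW was seen every time and that every record was mis-scored.
- **That different weeks were mixed within a cycle.** Nothing suggests that CHWs were visited on different schedules.
- **That two checklists were in use.** Tables 4 and 5 hold focus-group questions, and the other two sections cite or point to Table 2. The reference is a numbering slip.
- **That reading times conflict in scoring.** Training teaches 20 minutes and the accuracy definition says 15, but the scored step is "Wait for 15–20 min before reading the POC-CCA test result", which both satisfy.
- **That containers were reused.** Training mentions "washing used urine containers using provided disinfectants", but washing and then discarding can be successive actions, and washing is not a scored step.

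**Conclusion.** The point holds in three respects: the timing of the first two observation cycles is not fixed, step 15 conflicts with the instruction to keep used kits, and two of the four parts of the safety definition are not on the checklist. If step 15 is scored literally, a compliant CHW can reach at most 14/15 (93.3%) overall and 6/7 (85.7%) on non-critical steps. The 90% rule is still met, but without room for another miss. These caps rest on literal scoring of step 15 as a single item, which the document neither confirms nor rules out. The primary comparison of treatment coverage is not affected. The correction should be made, since the analysis is described as still to come.

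**What to change.** 1. State the visit weeks actually used, and analyse by weeks since training rather than by cycle number alone.
2. Reconcile step 15 with the instruction to keep kits, so that retaining a kit for collection is not scored as an error. If step 15 was recorded as one combined item for gloves, desiccant, wrappers and kits, the kit part cannot be separated afterwards. In that case, report the 90% outcome with and without step 15.
3. Align the safety definition with the items recorded in Table 2, and say that disposal of containers and urine was not scored by the checklist.
4. As minor corrections, cite Table 2 in place of Tables 4 and 5 in the assessment section, and reconcile the passages on urine containers and on reading time. This review does not choose between those versions.

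The cost is wording and some analysis work. No new data are needed, provided the dates of training and of visits were kept.

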### Data management and analysis

Some parts of the open checklist were coded before entered in the computer for analysis. Collected data were double entered using CSPro and the final data set were stored in MySQL database. Data were screened for consistency and errors corrected. Data analysis will be done using Stata version 15 (Stata Corp, College station, Texas, USA). Descriptive statistics will be used to describe participant’s demographic information. Assessment of uptake of praziquantel treatment will be done by comparing proportion of the outcomes between clusters in the two arms. For the intervention arm, treatment coverage will be assessed based on number of individuals tested and received treatment after diagnosis as registered in the booklets. For the control arm, coverage for praziquantel treatment will be assessed from the CHWs booklets/registers.

Odds ratios (OR) and 95% confidence interval (CIs) will be calculated using random effect logistic regression analysis adjusting for clustering. For assessing safety and accurate use of CCA test by CHWs, percentage of total steps, crucial steps and no-crucial steps performed correctly will be calculated for each observation cycle and a generalized estimating equation (GEE) logistic regression model for panel data will be fitted to identify factors associated with correct performance of at least 90% of the total steps. In addition, pooled mean and median percentage for reading of the 20 photographic results will be calculated for each observation cycle.

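### The checklist for community health workers has no item for two of the four elements that define safety, and no safety score is planned, so a visit can fail both and still score 100%

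*Protocol article*

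**What the plan says.** The definition stands in the Methods subsection on assessing safety and accuracy of the CCA test: "Safety was defined as correctly wearing gloves, use of new urine container for every participant and disposal of the urine containers in approved buckets". The sentence goes on to a fourth element, "urine samples in the toilet immediately after use". The same subsection says the steps were divided into a safety part and an accuracy part.

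The instrument is Table 2. The Trial summary names it for judging compliance with safety procedures. The subsection on training laboratory technicians says workers were assessed "using a standardized checklist (steps of test preparation and safety measures) as shown in Table 2". Table 2 prints 15 numbered steps, with the most critical ones in bold. The items nearest to the safety definition are:

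- Step 2 (bold): gloves.
- Step 3 (not bold): "Provide participants with new urine container (s) and instruct them on how to collect urine sample(s) using the provided container".
- Step 9 (bold): disposal of the used pipette.
- Step 15 (not bold): "Dispose of used gloves, desiccant, wrappers and used test kits".

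For the analysis, Data management and analysis says that "percentage of total steps, crucial steps and no-crucial steps performed correctly will be calculated for each observation cycle". It adds a GEE logistic model for factors associated with performing at least 90% of all steps correctly, and a summary of readings of 20 photographed tests.

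**The concern.** Safe use of the test by community health workers is both a secondary objective and a secondary outcome, and the Discussion says the study will demonstrate it. That conclusion would rest on the step percentages. If the checklist does not record part of what the article calls safety, a high percentage cannot support the whole claim.

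Two features combine. The checklist lacks items for part of the definition. The planned summaries also group steps as critical or not, rather than as safety or accuracy. Even the safety elements that are on the checklist are therefore never reported as a safety result.

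**Working it through.** **Step 1: map the four safety elements to Table 2.**

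| Safety element | Table 2 item | Bold (critical)? |
|---|---|---|
| Gloves | Step 2 | Yes |
| New container for every participant | Step 3 | No |
| Containers into approved buckets | None | – |
| Urine into the toilet | None | – |

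The only disposal items are step 9 (pipette) and step 15 (gloves, desiccant, wrappers, kits). After the urine is drawn at step 8, no step deals with the container or the remaining urine.

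**Step 2: count the denominators.** Bold steps are 2, 5, 6, 8, 9, 10, 11 and 12, so there are 8 critical and 15 − 8 = 7 non-critical steps. The 90% outcome needs at least 0.90 × 15 = 13.5, that is 14 of 15 steps.

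**Step 3: score visits in which everything not named is done correctly.**

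| What fails | Critical | Non-critical | Total | Meets 90%? |
|---|---|---|---|---|
| Both disposal elements | 8/8 = 100% | 7/7 = 100% | 15/15 = 100% | Yes |
| Both disposals and container reused | 8/8 = 100% | 6/7 = 85.7% | 14/15 = 93.3% | Yes |
| Gloves only | 7/8 = 87.5% | 7/7 = 100% | 14/15 = 93.3% | Yes |

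The first row is the core of the point: two of four safety elements fail and no planned summary moves. In the second row three of four fail, and only the non-critical and total percentages register it, through the reused container.

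**Step 4: would adding the two items be enough?** With 17 items, the 90% outcome needs at least 0.90 × 17 = 15.3, that is 16 steps. A visit failing both disposals scores 15/17 = 88.2% and no longer passes. A visit failing one safety element scores 16/17 = 94.1% and still passes. A separate safety summary is needed as well.

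**Step 5: how often could this happen?** The document gives no disposal rates. If each disposal element were done correctly with probability p, independently of the other and of the listed steps, a share 1 − p² of visits would breach disposal without any score changing: 36% at p = 0.80, 19% at p = 0.90 and 9.75% at p = 0.95. These figures only restate the assumed p and are not estimates for this trial.

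**The case against.** **No bias has been shown.** This stands. If every step and element were done correctly with the same probability, the expected percentage would be the same for the 8 critical steps, the 15 steps and the four safety elements. A reader might infer that reported safety is biased upward. That requires disposal to be done worse than the listed steps, and nothing in the document says so.

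**Some breaches do lower scores.** This also stands. A reader might infer that any unsafe visit scores 100%, or that no container breach can count. Reuse costs step 3, and a glove failure gives 7/8 on critical steps. Only the two disposal elements leave every score untouched.

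**The 90% rule is not a safety threshold.** Correct: it defines the outcome of a model for associated factors. The point is about which items are scored, not about the cut-off.

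**Accuracy does not rest on the checklist alone.** Correct: workers also read 20 photographs, and used kits are re-read. Neither source says anything about disposal of urine or containers.

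**An article condenses, and a fuller field checklist may have recorded disposal.** This is possible; the analysis section mentions coded parts of an open checklist. But the article prints a complete numbered list, names it as the safety instrument, and defines safety in terms that the list does not cover. That is a mismatch between two printed statements, not a detail left to another document. The assessment subsection's own pointer to Tables 4 and 5 does not help, since those are focus group question guides without safety steps.

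**Conclusion.** The point holds in a limited form. Two of the four elements that define safety have no item on the printed checklist, and the planned analysis forms no safety score although the steps are said to be split into safety and accuracy parts. A visit can fail both disposal elements and score 100% on every planned step summary. With container reuse added, it still scores 93.3% in total and meets the 90% outcome. These results need no assumption beyond Table 2 being the checklist used.

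The direction and size of any error in reported safety are not established. They depend on how often disposal fails, which the document does not give. What can be said is that the planned summaries cannot support a safety conclusion covering all four elements.

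Two related statements also need attention. The assessment subsection cites the wrong tables for the checklist. The training subsection describes washing used urine containers with disinfectant, which sits badly with the wording on new containers and their disposal.

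**What to change.** 1. In Data management and analysis, keep the existing summaries and add a separate safety summary for each observation cycle: the share of visits with all recorded safety elements correct.
2. If disposal of containers and of urine was recorded, or can still be, add both as Table 2 items and include them in that summary. State whether the 90% outcome is then computed on 15 or 17 steps.
3. If disposal was not recorded, limit the safety conclusion to gloves and new containers, and state that disposal was not assessed. Observation is described in the past tense, so this may be the realistic route.
4. If an accuracy score is also formed, keep labelling steps 5 and 6 in it. The accuracy definition opens by requiring all steps needed for a correct diagnosis, and a mislabelled kit can send a result to the wrong person.
5. Correct the checklist reference from Tables 4 and 5 to Table 2, and reconcile the training text on washing containers with the safety definition.

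The cost is analysis wording and, at most, two extra checklist entries per visit. The downside is a narrower or less favourable safety statement for a secondary outcome.
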